# The efficacy of virtual reality technology for the postoperative rehabilitation of patients with cervical spondylotic myelopathy (CSM): a study protocol for a randomized controlled trial

**DOI:** 10.1186/s13063-024-07962-9

**Published:** 2024-02-19

**Keywords:** Virtual reality technology, Cervical spondylotic myelopathy, Postoperative rehabilitation, Brain plasticity, Randomized controlled trial

## Abstract

**Background:**

Patients with cervical spondylosis myelopathy (CSM) may experience severe neurological dysfunction due to untimely spinal cord compression after surgery. These disorders may lead to sensory and motion disorders, causing considerable psychological distress. Recent studies found that virtual reality (VR) technology can be an effective tool for treating spinal cord injuries. Owing to this discovery, we developed an exploratory research project to investigate the impact of this intervention on the postoperative recovery of patients with CSM.

**Methods:**

The purpose of this randomized controlled trial was to evaluate the efficacy of combining VR technology with conventional rehabilitation strategies for the postoperative rehabilitation of patients with CSM. A total of 78 patients will be recruited and randomized to either the conventional rehabilitation group or the group subjected to VR technology combined with conventional rehabilitation strategies. The Japanese Orthopaedic Association (JOA) scale will be the main tool used, and secondary outcomes will be measured via the visual analogue scale (VAS), neck disability index (NDI), and functional MRI (fMRI). The data analysis will identify differences between the intervention and control groups as well as any relationship between the intragroup changes in the functional area of the brain and the subjective scale scores after the intervention.

**Discussion:**

The aim of this trial is to investigate the effect of VR training on the postoperative rehabilitation of patients with CSM after 12 intervention treatments. Positive and negative outcomes will help us better understand the effectiveness of the intervention and its neural impact. If effective, this study could provide new options for the postoperative rehabilitation of patients with CSM.

**Trial registration:**

Chinese Clinical Trial Registry (ChiCTR2300071544). Registered 17 May 2023, https://www.chictr.org.cn/.

**Supplementary Information:**

The online version contains supplementary material available at 10.1186/s13063-024-07962-9.

## Background

Cervical spondylotic myelopathy (CSM) is a spinal cord disease characterized by degenerative changes in the cervical spine, such as degenerative disc disease, ossification of the posterior longitudinal ligament (OPLL), and hypertrophy of the yellow ligament. These changes can cause the surrounding blood vessels and nerve structures to become compressed, thus leading to a range of sensory and motor symptoms. The clinical symptoms included limb weakness, gait instability, and diminished sensory and motor function. In severe cases, quadriplegia can occur. Moreover, CSM is more common in middle-aged and elderly individuals older than 55 years [1]. In North America, the incidence and prevalence of CSM are at least 41 and 605 per million people, respectively, while in East Asian countries, the hospitalization rate for patients with CSM is 4.04 per 100,000 person-years [2, 3]. With social progress, technological advancements, and changes in human lifestyles and work patterns, the incidence of CSM is increasing annually, particularly in young people [4]. Surgery is the most effective treatment for patients with middle and advanced stage disease [5]. However, some postoperative CSM patients still experience sensory and motor disorders, such as lower limb weakness, gait instability, and numbness, which need to be addressed. With the development of neuroimaging, researchers studying brain plasticity found that CSM could lead to brain plasticity, which plays an important role in functional recovery after surgery for CSM [6]. A deeper understanding of the development of CSM-related brain plasticity is highly important for developing appropriate rehabilitation plans and improving clinical efficacy.

The central nervous system (CNS) has been confirmed to be able to reorganize structurally and functionally after injury, enabling repair through neuroplasticity [7]. Brain plasticity is the brain’s ability to modify its structure and function to adapt to environmental changes and experiences [8]. Researchers revealed that the recovery of neural function in CSM patients depends on both spinal cord compression and injury as well as brain function reorganization or plasticity [9]. Moreover, cortical plasticity compensates for some function by involving brain regions that are not primarily involved in a specific task [10]. Therefore, when spinal cord injury occurs, cortical plasticity also occurs. Sabbah, P. et al. discovered that cortical reorganization, either physically or via mental imagery, could activate the lower limb cortical network years after injury and is therefore an adaptive remodelling response known as cortical-spinal neural plasticity [11]. Liu, M. et al. conducted a study using volumetric magnetic resonance imaging (MRI) with voxel-based morphometry (VBM) on 41 CSM patients both before and after surgery and compared the VBM measurements to those of a control group [12]. They assessed the changes in the cortical grey matter volumes in CSM patients before and after surgery and found that, compared to those in the control group, the grey matter volumes in the left caudate nucleus and the right thalamus were lower in the preoperative CSM patients. Six months after surgery, the bilateral grey matter volume in the posterior cerebellar lobes decreased in the postoperative CSM patients, while the grey matter volume in the brainstem was greater than that in the preoperative CSM patients. Compared to the control group, the postoperative CSM patients in the present study had a significantly lower grey matter volume in the left caudate nucleus but higher grey matter volumes in the right inferior temporal gyrus, right orbitofrontal cortex (OFC), and bilateral lingual gyri/cuneus/precuneus cortex. Therefore, based on the scientific theory of brain plasticity, it is important to select appropriate methods to regulate the CNS and promote spinal cord recovery after surgery to ensure the smooth rehabilitation of CSM patients. In recent years, VR technology has been increasingly applied in clinical treatment, particularly for incomplete spinal cord injury, stroke, Parkinson’s disease, and other areas, to promote rehabilitation through brain remodelling [13–15]. This technology could also be a potential therapeutic option for CSM patients after surgery.

VR technology is a tool that allows users to create and experience computer-generated 3D environments and interact with various objects in real time through visual, auditory, or tactile feedback. VR is a simulated 3D interactive system with dynamic scenes and entity behaviours that allows the integration of multiple sources of information such as scene displays, force/tactile sensors, and position trackers. Motion training has shown promise in that patients can become immersed in virtual environments, thereby providing a pleasant and exciting experience for users. Multisensory stimulation provided by VR can potentially promote the reshaping and reconstruction of the central nervous system, improving gait instability. Kirsch, P et al. used fMRI technology to demonstrate that monetary rewards produced greater brain activation than verbal rewards, suggesting that the type of reward has a strong stimulating effect on brain activity [16]. Animal and human neuroimaging studies have shown that reward delivery is associated with the activation of the subcortical edge and anterior brain areas, including the substantia nigra, thalamus, striatum, orbital frontal cortex, insula, and precentral gyrus. The activation of these relevant brain regions through the reward system may lead to brain reshaping. The degree of motor function recovery depends on the extent of neural population reshaping induced by the intervention. Neuroimaging studies have demonstrated that VR can induce cortical reshaping of motor pathways, including the primary sensory motor cortex, SMA, cerebellum, precentral gyrus, and ipsilateral and contralateral marginal gyri, through visual, auditory, and tactile feedback [17]. This approach creates a realistic environment and provides a safe and stimulating learning environment for subjects. By stimulating brain plasticity through a large number of movement repetitions and multisensory methods, brain reshaping mechanisms can be used to reconstruct gait.

### Study aim

The main objective of this randomized controlled trial was to evaluate the effectiveness of virtual reality technology in the postoperative rehabilitation of patients with CSM. The secondary objective was to explore the potential patterns of cortical plasticity related to sensory and motor function recovery in CSM patients via pre- and postintervention fMRI and longitudinal JOA studies to provide a theoretical basis for investigating the central role of virtual reality training in promoting brain plasticity in patients who have undergone surgery for cervical spondylosis.

## Method/design

### Study design

The aim of this randomized controlled trial was to investigate the effectiveness of virtual reality (VR) technology in the postoperative rehabilitation of patients with CSM. A total of 78 eligible patients were recruited and randomly assigned to either the routine rehabilitation group or the VR training combined with routine rehabilitation group (1:1). The primary outcome will be measured with the Japanese Orthopaedic Association (JOA) (Table 1) cervical myelopathy evaluation scale, and the secondary measures will include the visual analogue scale (VAS), neck disability index (NDI), and functional magnetic resonance imaging (fMRI) scans [18–20]. The intervention will be implemented in accordance with a standardized protocol, and independent researchers will execute and supervise the random allocation of patients in the trial. The study protocol is in compliance with the SPIRIT recommendation. For the SPIRIT checklist, see Additional file 1, and the study design is presented in Figs. 1 and 2. This study is an exploratory investigation.

**Table 1 Tab1:** Japanese Orthopaedic Association (JOA) score for patients with cervical myelopathic

Motor function	
Upper extremity	
The thumb and fingers	
0 [Complete disturbance] The patient cannot use chopsticks or a spoon/fork, and cannot fasten a button on his or her own.	
1 [Severe disturbance] The patient cannot use chopsticks or write, and can barely use a spoon/fork.	
2 [Moderate disturbance] The patient can pick up a large object with chopsticks but can hardly write. He/she can fasten a large button.	
3 [Slight disturbance] The patient makes awkward use of chopsticks, writes in a clumsy manner, but can fasten buttons on his/her shirt.	
4 [Normal] Normal	
Lower extremity	
0 [complete disturbance] The patient cannot stand or walk alone.	
(0.5 The patient can stand up.)	
1 [Severe disturbance] The patient needs support to walk on a flat surface.	
(1.5 The patient can walk on a flat surface without any support but the walking is not stable.)	
2 [Moderate disturbance] The patient can walk on a flat surface without any support, but needs a handrail to walk up and down stairs.	
(2.5 The patient can walk on a flat surface without any support, but needs a handrail only to walk down stairs.)	
3 [Slight disturbance] The patient can walk fast, although awkwardly.	
4 [Normal] Normal	
Sensory function	
Upper extremity	
0 [Severe disturbance] Complete sensory loss (touch sensation, pain sensation)	
(0.5 Partial sensory loss ≤ 5/10 (touch sensation, pain sensation); intolerable pain or numbness)	
1 [Moderate disturbance] Partial sensory loss ≥ 6/10 (touch sensation, pain sensation); numbness and hypersensitivity.	
(1.5 [Slight disturbance] Slight numbness (normal sensation))	
2 [Normal] Normal	
Trunk	
0 [Severe disturbance] Complete sensory loss (touch sensation, pain sensation)	
(0.5 Partial sensory loss ≤ 5/10 (touch sensation, pain sensation); intolerable pain and numbness)	
1 [Moderate disturbance] Partial sensory loss ≥ 6/10 (touch sensation, pain sensation); numbness and hypersensitivity.	
(1.5 [Slight disturbance] Slight numbness (normal sensation))	
2 [Normal] Normal	
Lower extremity	
0 [Severe disturbance] Complete sensory loss (touch sensation, pain sensation)	
(0.5 Partial sensory loss ≤ 5/10 (touch sensation, pain sensation); intolerable pain and numbness)	
1 [Moderate disturbance] Partial sensory loss ≥ 6/10 (touch sensation, pain sensation); numbness and hypersensitivity.	
(1.5 [Slight disturbance] Slight numbness (norm sensation))	
2 [Normal] Normal	
Urinary bladder function	
0 [Severe disturbance] Urinary retention, incontinence	
1 [Moderate disturbance] Feeling of residual urine, straining of oneself, dull urination, elongation of urination (retarded urination), urinary incontinence	
2 [Slight disturbance] Retarded urination, pollakisuria	
3 [Normal] normal	
Total 17

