#### Primary outcome measurement

The primary outcome measure was the change in the JOA score for the cervical spine. The JOA score consists of a total of 17 points, with 4 points each for upper and lower limb motor function, 2 points each for upper and lower limb and trunk sensation, and 3 points each for bladder function. Patients were assessed using the JOA score before intervention, after intervention, and during follow-up in accordance with the JOA evaluation criteria for cervical spine disease treatment established by the Japanese Orthopaedic Association. The results were categorized into five groups: > 75% excellent, 50–74% good, 20–49% fair, 0–19% no change, and < 0 deterioration.

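### As worded, Table 1 puts the two middle sensory grades of the primary-outcome scale in the wrong order, so a smaller partial loss scores lower than a larger one

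*Protocol article*

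**What the plan says.** The Study design section ties the primary outcome to the printed table: "The primary outcome will be measured with the Japanese Orthopaedic Association (JOA) (Table 1) cervical myelopathy evaluation scale". The section on the primary outcome measurement adds: "The primary outcome measure was the change in the JOA score for the cervical spine".

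For the upper-extremity sensory item, the bottom of the scale in Table 1 reads "0 [Severe disturbance] Complete sensory loss (touch sensation, pain sensation". Two grades for incomplete loss lie above it. The higher of the two, worth a full point, is worded "1 [Moderate disturbance] Partial sensory loss ≥ 6/10 (touch sensation, pain sensation); numbness and hypersensitivity". The lower of the two, worth half a point, is worded "0.5 Partial sensory loss ≤ 5/10 (touch sensation, pain sensation); intolerable pain or numbness". At the top of the item come 1.5 for slight numbness with sensation intact and 2 for normal. The trunk and lower-extremity items carry the same fractions in the same order.

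For the bladder, the lowest grade is "0 [Severe disturbance] Urinary retention, incontinence". Grade 1 ends with "elongation of urination (retarded urination), urinary incontinence", and grade 2 lists retarded urination again.

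The section on the primary outcome measurement then gives percentage bands: "The results were categorized into five groups: > 75% excellent, 50–74% good, 20–49% fair, 0–19% no change, and < 0 deterioration". It prints no formula for the percentage.

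**The concern.** With complete loss at 0 and normal at 2, the score should never fall as less sensation is lost. Between the two middle grades it does. The three sensory items hold 6 of the 17 points, and the score enters the trial in three places: as the primary outcome, as an eligibility criterion (5 to 15), and in the planned correlation of imaging with sensory and motor recovery. If raters work from the printed wording, some real sensory improvements would be entered as deterioration, and some deteriorations as improvement.

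The bladder grades raise a lesser problem. A patient whose only symptom is incontinence, or only retarded urination, fits two adjacent grades, so the rater has one point of choice.

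**Working it through.** **Inputs.** Item grades and maxima come from Table 1 and the primary outcome section, the baseline range of 5 to 15 from the inclusion criteria, and the bands from the primary outcome section.

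**Plan's own figure.** The item maxima are 4 + 4 + 2 + 2 + 2 + 3 = 17, which matches the printed total. The sensory share is 2 + 2 + 2 = 6.

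**Sensory score by tenths lost.** The last column swaps the two middle rows, for comparison only.

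| Tenths lost | As printed | Middle rows exchanged |
|---|---|---|
| 10 (complete) | 0 | 0 |
| 6–9 | 1 | 0.5 |
| 1–5 | 0.5 | 1 |
| 0 | 1.5 or 2 | 1.5 or 2 |

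The printed column goes 0, 1, 0.5, then 1.5 or 2, so it is not monotone. The exchanged column is.

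**Change scores per region.**

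- From 6–9 to 1–5 tenths lost: printed 0.5 − 1 = −0.5; exchanged 1 − 0.5 = +0.5. The direction is reversed.
- From complete loss to 6–9: printed +1; exchanged +0.5. Direction right, size off by 0.5.
- From complete loss to 1–5: printed +0.5; exchanged +1. Direction right, size off by 0.5.
- From 6–9 to normal: printed 2 − 1 = +1; exchanged 2 − 0.5 = +1.5. Direction right, size off by 0.5.
- From 1–5 to normal: printed 2 − 0.5 = +1.5; exchanged 2 − 1 = +1. Direction right, size off by 0.5.

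So only a crossing between the two middle grades changes sign. The largest case for one patient is that crossing in all three regions: 3 × (−0.5) = −1.5 as printed, against 3 × 0.5 = +1.5 in the exchanged order.

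**Possible origin.** The printed order would be coherent if the fractions meant sensation retained: retaining at most 5/10 would score 0.5, and retaining at least 6/10 would score 1. The text says loss. The two repairs differ at exactly five tenths lost (1 if the rows are exchanged, 0.5 if the fraction is retained sensation), so the source scale has to settle it.

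**Bladder.** Incontinence appears in grades 0 and 1, and retarded urination in grades 1 and 2. Each shared symptom, taken alone, can be graded two ways, one point apart.

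**Bands.** Exactly 75% is neither above 75 nor within 50–74, and rounding to whole percent does not help. The formula is not printed, so two were assumed. All baselines from 5 to 15 were paired with every follow-up score from baseline to 17 in half points (315 pairs).

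- Gain / (17 − baseline): exactly 75% arises in 6 pairs: 5→14, 7→14.5, 9→15, 11→15.5, 13→16 and 15→16.5. For example, (15 − 9)/(17 − 9) = 6/8 = 75%.
- Gain / baseline: exactly 75% arises in 2 pairs, 6→10.5 and 8→14.
- Under either formula no pair falls between 49 and 50 or between 74 and 75. The few between 19 and 20, such as 6.5→8.5 at 2/10.5 = 19.05%, round to 19.

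**The case against.** The strongest reply is that a misprint in an article does not show that any patient was mis-scored. The primary outcome section says assessment follows the criteria set by the Japanese Orthopaedic Association, and the raters' form is not shown. The remaining words in the two middle grades also run the right way: intolerable pain sits at 0.5, and the milder numbness with hypersensitivity sits at 1 under a moderate label. A rater therefore has cues to the intended order. All of this stands, and it makes the harm conditional. It does not make the printed rule right: the same fractions appear in all three items, and the article names this table as its instrument.

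A reader might set the 1.5-point figure against the pilot difference of 15.30 − 14.7 = 0.6 and infer that the treatment effect could be swamped or reversed. The documents do not support that. One figure is a worst case for a single patient and the other is a difference between group means. That patient would have at most 1.5 of the 6 sensory points at follow-up, so a printed total of no more than 17 − 4.5 = 12.5. This lies (14.7 − 12.5)/0.78 = 2.8 SD below the conventional-arm pilot mean and (15.30 − 12.5)/0.90 = 3.1 SD below the VR-arm mean. Both arms also use the same table.

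A reader might also infer that the overlapping bladder grades are exploited by raters who know the allocation. The Blinding section does say evaluators were not blinded, but Data collection and management and the Discussion say outcome assessors are blinded, so that premise is not established. The repeated bladder symptoms stand under different severity labels and may be meant as degrees of one symptom. That argues for checking the source rather than redesigning the scale.

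Finally, the bands enter no stated analysis. The Statistical analysis section compares continuous outcomes by t test or Mann–Whitney test. That objection stands in full.

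**Conclusion.** The point holds as an error in the printed scoring rule. In all three sensory items of the instrument named for the primary outcome, a partial loss of 6/10 or more scores 0.5 higher than one of 5/10 or less. If raters follow that wording, a patient who improves across the line is recorded as 0.5 worse per region instead of 0.5 better, and at most 1.5 worse over three regions.

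The effect on arm means cannot be derived from the documents. It depends on how many patients cross that line and on whether the case report form repeats the wording. It would be wrong to conclude that trial data have already been mis-scored.

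The bladder overlap is real and secondary. The gap at exactly 75% is real and minor, because the bands are descriptive and leave the primary analysis of JOA change untouched. The point should be corrected while recruitment continues, but it does not call the design into question.

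**What to change.** 1. Reconcile Table 1 and the case report form with the source instrument, so that a smaller loss never scores lower than a larger one. If the fractions are meant as sensation retained, say so.
2. Confirm which wording raters have used since recruitment began on 7 June 2023, and brief them on the reconciled version.
3. Check the forms already completed. Re-score where the recorded findings allow it; where only the grade was recorded, document that re-scoring is not possible.
4. In the same check, reconcile the bladder grades with the source for incontinence and retarded urination.
5. Make the percentage bands contiguous, for example ≥ 75, 50 to < 75, 20 to < 50, 0 to < 20 and < 0. State the formula and label the bands as descriptive.

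The cost is a correction to the table and form, a short briefing and a review of completed forms. Sample size and the planned tests do not change.

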**Fig. 1 Fig1:**
[figure not shown]
Flow chart of study design

**Fig. 2 Fig2:**
[figure not shown]
The schedule of enrolment, interventions, and assessments. Abbreviations: JOA, Japanese Orthopaedic Association; NDI, Neck Disability Index; VAS, visual analogue scale; fMRI, functional magnetic resonance imaging

### Participants

The aim of this study was to recruit 78 patients who underwent surgery for CSM, with JOA scores between 5 and 15 and aged between 20 and 75 years. All eligible participants will be recruited from the orthopaedic and rehabilitation medicine departments of our hospital and other hospitals. The study was conducted at multiple centres, including Shanghai Longhua Hospital, Affiliated with Shanghai University of Traditional Chinese Medicine, and Shanghai Shuguang Hospital, Affiliated with Shanghai University of Traditional Chinese Medicine. Both of these hospitals are located in Shanghai, China. Prior to the experiment, we provided a comprehensive explanation of the study’s purpose, type of intervention, and potential risks and benefits of using VR technology to the participants who consented to participate. We will respect their decision to withdraw from the study at any time for any reason. At the same time, we maintained regular contact with participants, created incentives, provided personalised designs, simplified experiment procedures, and increased communication and engagement to increase loyalty and participation and to ensure that the experiment would be successful.

